### Exclusion Criteria

• Patients less than 18 years of age, or unable to give informed consent

• Laparoscopic-assisted cases

• Previous laparotomy within the past 3 months

### Primary outcome measure

The primary outcome is Surgical Site Infection (SSI) within 30 days of surgery.

Positive identification of SSI will be determined with use of the internationally accredited Centers for disease Control and Prevention (CDC) definitions.

We hypothesise that the use of wound-edge protection device in adults undergoing laparotomy will result in a reduced rate of surgical site infection of 50% based on evidence from Horiuchi et al, 2007 [12].

The power calculations for a range of baseline infection rates and this assumed 50% reduction in SSI rate brought about by use of the device are shown in table 2.

**Table 2 T2:** Infection rates and sample size

Infection rate in untreated group	Expected infection rate in treated group	Overall sample size	Sample size in each arm
18%	9%	448	224

15%	7.5%	554	277

12%	6%	**710**	**355**

(80% power and 0.05 significance level)

A conservative estimate of infection rate of 12% requires a total of 710 patients, randomised 1:1 between treatment and placebo. Thus we intend to recruit 750 patients in total in order to provide adequate power should our assumptions informing the power calculation prove optimistic, and to accommodate a potential 5% dropout rate.

### Secondary Outcomes

Comparisons will be made to assess the impact of treatment relating to the following outcomes:

1) The degree of wound contamination (e.g. colorectal resections/vascular surgery)

2) Presence of major comorbidity (e.g. diabetes, obesity, smoking)

3) Health-related quality of life (QoL) to be assessed using the EQ-5D questionnaire

4) Length of stay in hospital

5) Health care utilisation and the incremental cost-effectiveness of the use of the wound-edge protection device compared to standard care

6) Adverse events

### Randomisation

The most important factor in determining risk of SSI is the type of surgery performed via the laparotomy wound and resulting degree of contamination. The standard categorisation and corresponding normal infection rates [18] are shown in table 3.

**Table 3 T3:** Classification of potential surgical contamination

Type of Surgery	Examples	**Normal Infection Rate (%) **[18]
Clean (no viscus opened)	Adhesiolysis	1-2

Clean-contaminated (viscus opened, minimal spillage)	Right Hemicolectomy, Open Cholecystectomy	< 10

Contaminated (open viscus with spillage or inflammatory disease)	Colectomy with some spillage Resection of active Crohns disease	15-20

Dirty (pus or perforation, or incision through an abscess)	Diverticular perforation	< 40

Randomisation will therefore be stratified according to degree of contamination using a minimisation procedure following the methods proposed by Pocock and Simon (1975) [19] using a programme developed by [name], University of Birmingham.

Please refer to the randomisation notepad (Additional file 1 Table S1) for details of operation-specific information to be collected prior to randomisation.

### Data Management

This is being supported by the Primary Care Clinical Trials Unit at the University of Birmingham. Data will be stored securely as a hard copy version and on computerised data bases (ACCESS).

### Statistical analysis

All analyses will be pre-specified and conducted according to the intention-to-treat principle with the use of SAS software (version 9.1, SAS Institute). P values other than for the primary end point are nominal.

#### Analysis of Primary and Secondary Outcomes

The primary outcome will be analysed using generalised linear models, with logit link, binomial error and with surgeon as random effects. Odds ratio 95% CI and p value will be presented. Continuous data will be analysed with the use of mixed models, which include surgeons as random effects [20]. The rates of adverse events shall be compared between groups by means of Fisher's exact test.

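### The primary model does not name contamination class, the factor on which allocation is minimised; adding it restores the nominal test size and gains a little power

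*Protocol article*

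**What the plan says.** Protocol article, Randomisation: "The most important factor in determining risk of SSI is the type of surgery performed via the laparotomy wound and resulting degree of contamination". Table 3 in that section gives normal infection rates of 1-2% (clean), under 10% (clean-contaminated), 15-20% (contaminated) and under 40% (dirty). It follows that "Randomisation will therefore be stratified according to degree of contamination using a minimisation procedure". Study Design also lists stratification by baseline infection risk as a design feature.

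Protocol article, Analysis of Primary and Secondary Outcomes, gives the model as follows: "The primary outcome will be analysed using generalised linear models, with logit link, binomial error and with surgeon as random effects". An odds ratio with 95% CI and p value is to be reported. Continuous outcomes get mixed models that also include surgeons as random effects. Contamination class appears in neither model.

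Covariates enter only under Exploratory analysis on the primary outcome. That is a stepwise model, fitted only if the primary result is significant.

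**The concern.** Minimising on a strong predictor removes most of the chance difference between arms in that predictor. The treatment comparison then varies less from trial to trial than under simple randomisation. A model without the predictor does not know this: it still counts the between-class variation as noise, so its standard error is too large. The confidence interval is somewhat too wide, the p value somewhat too large, and some power is given up although the class is already held at randomisation.

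The exploratory model cannot repair this, because it is fitted only once the primary test has succeeded. The surgeon effect is a different term: surgeons can operate across several classes, and surgeon is not named as a minimisation factor.

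**Working it through.** **1. Reproduce the plan's sample size.** Inputs from Primary outcome measure: 12% against 6%, 80% power, significance level 0.05. Two-sided test, pooled variance under the null:

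n = [1.96·√(2·0.09·0.91) + 0.8416·√(0.12·0.88 + 0.06·0.94)]² / 0.06² = (0.7932 + 0.3387)² / 0.0036 ≈ 356 per arm.

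Table 2 has 355. The other rows give 278 and 226 against 277 and 224. The plan's figures are therefore those of an unadjusted comparison of two proportions; at 355 per arm the formula gives 79.9% power.

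**2. Size of the test without the class, by formula.** With arms balanced within classes of share w and infection rate p, the ratio of true to assumed variance under the null is

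r = Σ w·p(1−p) / [0.12·0.88],

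and the true two-sided level of a nominal 5% test is 2·[1 − Φ(1.96/√r)].

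Example: shares 20/50/15/15% (clean, clean-contaminated, contaminated, dirty), rates 1.5/7.2/18.0/36.0%. With unrounded rates, the numerator is 0.00304 + 0.03339 + 0.02213 + 0.03455 = 0.0931. So r = 0.0931/0.1056 = 0.882, 1.96/√0.882 = 2.087, and the true level is 3.7%.

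**3. Range over assumed case-mixes, by formula and simulation.** The case-mix is not in the article. Five mixes were tried, with class rates in or near Table 3 and rescaled to a 12% control average. The simulation used biased-coin minimisation on the four classes (probability 0.8, assumed), N = 710, a halved rate in every class under the alternative, Wald tests from logistic regression and 14,000 replicates. Monte Carlo standard error is about 0.2 points for type I error. Surgeon was left out of both models here.

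| Shares, % | Control rates, % | r | Level by formula | Simulated level, without / with class | Simulated power, without / with class |
|---|---|---|---|---|---|
| 5/70/20/5 | 2.1/10.2/17.1/26.8 | 0.978 | 4.75% | 4.9 / 5.2% | 80.1 / 80.7% |
| 15/60/20/5 | 1.8/9.3/20.4/40.9 | 0.928 | 4.2% | 3.9 / 4.7% | 80.4 / 82.0% |
| 15/50/20/15 | 1.5/7.9/17.2/29.4 | 0.928 | 4.2% | 4.4 / 5.4% | 80.9 / 82.6% |
| 20/50/15/15 | 1.5/7.2/18.0/36.0 | 0.882 | 3.7% | 3.5 / 4.8% | 80.9 / 83.4% |
| 30/40/10/20 | 1.5/5.9/17.2/37.4 | 0.830 | 3.1% | 3.2 / 5.1% | 81.5 / 85.3% |

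Rescaling takes some rates in the first two rows slightly outside Table 3; the last three rows lie within it. Likelihood-ratio tests show the same pattern.

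**4. Does the surgeon effect replace the class?** A smaller simulation fitted random-intercept logistic models (40 surgeons, surgeon SD 0.3, case-mix differing mildly or strongly between surgeons, N = 710, 2,500 replicates, all assumed). With shares 10/60/20/10%, the level was 3.9% and 3.6% without class, and 4.8% and 4.5% with it; power was 82.0% and 81.8% against 83.8% and 83.4%. With shares 20/45/20/15%, the level was 3.9% and 4.2% against 5.6% and 5.8%; power was 79.7% and 80.6% against 83.4% and 83.6%. Monte Carlo standard errors are about 0.4 and 0.8 points, and the second mix sets the dirty class at 40%, the bound in Table 3. This is indicative only, but the power gain of 1.6 to 3.7 points remains with surgeon in the model.

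**5. Sparse clean class.** With n clean patients split equally, control risk p and a halved risk with the device, the chance of no clean-class event is (1−p)^(n/2)·(1−p/2)^(n/2). For 712 evaluable patients (750 less 5%), a 10% clean share and p = 1.5%, n is about 71. About 0.8 events are expected, and the chance of none is 45%. A 15% share at 1.5% gives 30%; a 20% share at 1% gives 34%.

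**The case against.** The strongest objection is that the sentence on the primary model is incomplete. It lists no fixed effects at all, not even treatment, and a journal article may leave the covariate list to the full protocol or analysis plan, which are not shown. The Statistical analysis section also says that all analyses will be pre-specified. This stands in part: nothing says the class will be left out deliberately, and a fuller document may include it. But the article does name link, error distribution and one additional term, and that term is not the factor it minimises on. Recommending the better model is fair on that text.

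The size can also be challenged, and this stands. Study Process, step 2, places allocation after induction of anaesthesia and before the operation. Table 3 separates "Clean-contaminated (viscus opened, minimal spillage" from "Contaminated (open viscus with spillage or inflammatory disease" partly by spillage, which may not be known then. If the anticipated class predicts infection less well than Table 3 suggests, the effect moves towards the weak end, where it is close to nil.

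A reader might infer that the primary test is invalid or the trial underpowered. The documents do not support that. The error is in the conservative direction, and Table 2 was computed without adjustment, so the planned power does not depend on the class being in the model.

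**Conclusion.** The point holds as a recommended improvement. The design balances on the strongest stated predictor of infection, and the stated primary model does not name it. Without the class, type I error is about 3% to 5% instead of 5%, and about 0.5 to 4 points of power are forgone. Type I error is not inflated, and power stays at about the planned 80%.

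The direction is secure provided that the class entered at randomisation predicts infection. The size is a range: it rests on assumed case-mixes, error-free classes, an assumed minimisation probability and, for the surgeon effect, one smaller simulation.

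**What to change.** Suggested text: *The primary outcome will be analysed by mixed-effects logistic regression with treatment and contamination class, as entered at randomisation, as fixed effects and surgeon as a random effect.* Use the same fixed effect in the mixed models for continuous outcomes. Use the class entered at randomisation, not the one found at operation, because the former is what allocation was balanced on.

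Add a rule for sparse classes: clean is pooled with clean-contaminated if it has no or very few events. Set the threshold in advance and apply it to the count over both arms combined. Without such a rule the clean-class coefficient may have no finite estimate and the model may not converge.

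The cost is a few sentences, with no new data or patients. The odds ratio becomes conditional on class. The planned rates give a marginal odds ratio of (0.06/0.94)/(0.12/0.88) = 0.47; in case-mixes of this kind the conditional one is about 0.42 to 0.44. That shift is a change of target and not a larger effect, so label the odds ratio as conditional and report an adjusted risk difference beside it.

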## Background

Surgical site infection (SSI) is one of the most common postoperative complications and occurs in at least five percent of all patients undergoing surgery [1]. The rate of SSI is significantly higher after open abdominal surgery which can carry an SSI risk of up to 40% depending on the level of contamination [2].

SSI is associated with considerable morbidity and it has been reported that over one-third of postoperative deaths are related, at least in part, to SSI [3]. It must be appreciated, however, that the diagnosis covers a wide spectrum of clinical conditions ranging from a relatively trivial wound discharge with no other complications to a life-threatening condition. Other clinical outcomes of SSI include poor scars that are cosmetically unacceptable, such as those that are hypertrophic or keloid, persistent pain and itching and a significant impact on emotional wellbeing [4].

SSI can double the length of time a patient stays in hospital and thereby increase the costs of health care. Additional costs attributable to SSI of between £814 and £6626 per case have been reported depending on the type of surgery and the severity of the infection [5,6]. The main additional costs are related to re-operation, extra nursing care and interventions, and drug treatment costs. The indirect costs, due to loss of productivity, patient dissatisfaction and litigation, and reduced quality of life, have been studied less extensively.

Recent national guidelines concerning the prevention and treatment of SSI have been issued by the National Institute for Health and Clinical excellence (NICE) [7]. These recommendations are based on systematic reviews of best available evidence, or when minimal evidence is available the guideline development group's opinion of what constitutes good practice. Intra-operative guidance includes the role of hand decontamination, sterile gowns and drapes and antiseptic skin preparation. Wound-edge protection devices are not discussed in these guidelines, presumably due to the paucity of published research into their use and efficacy in the prevention of infection

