### Trial Management Protocols

Two named principle investigators (PI) will be recruited at each study site. Together they shall provide blinded wound reviews for the other PI's patients by being unaware of which arm of the study these patients belong to. The two wound reviews will occur firstly prior to discharge at day 5 to 7 post-operation and then a formal outpatient appointment or ward attendance for wound review will be arranged at or just after 30 days (day 30-33 post-operation). At this visit patients will also be asked to complete a retrospective questionnaire regarding their wound and its healing over the intervening period. This will ensure that full information is gathered about any wound infections, together with resulting treatment or hospital admissions, occurring between the day 5-7 and day 30-33 reviews. Enrolled patients will also be given contact details for the local primary investigator should any concerns by raised by the patient. Wound assessment at both stages will utilise a standardised proforma. These wound assessment tools will be pre-validated for reproducibility and ease-of-use in a pilot study to be ran prior to full trial launch.

QOL data will be assessed using the EQ-5D pre-operatively, at 5-7 days, at the 30-33 day follow-up visit.

We also envisage the involvement of clinical nurse specialists at most sites. Their clinic appointments are generally more accessible and it may be feasible to utilise these for the second formal (outpatient) wound review. Clinical nurse specialists are generally experienced in assessing post-operative wounds themselves and they may also therefore provide a second-line cohort of blinded wound reviewers if the relevant PI is not available.

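### The stated model for continuous secondary outcomes names no baseline term, although EQ-5D is measured before surgery; naming it would sharpen the EQ-5D comparison at no cost

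*Protocol article*

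**What the plan says.** The section Analysis of Primary and Secondary Outcomes covers all continuous outcomes in one sentence: "Continuous data will be analysed with the use of mixed models, which include surgeons as random effects". It lists no fixed effects.

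The Secondary Outcomes section includes "Health-related quality of life (QoL) to be assessed using the EQ-5D questionnaire". Trial Management Protocols gives the schedule: "QOL data will be assessed using the EQ-5D pre-operatively, at 5-7 days, at the 30-33 day follow-up visit". A pre-operative score on the same scale is therefore available.

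The Randomisation section describes minimisation and names one factor, the contamination class of the surgery. Inclusion Criteria admits both elective and emergency laparotomy.

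The Statistical analysis section adds two general statements: "All analyses will be pre-specified and conducted according to the intention-to-treat principle" and "P values other than for the primary end point are nominal".

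**The concern.** A pre-operative measurement of the outcome is usually among the strongest predictors of its later value. Here it is collected anyway, but the one modelling sentence that applies names only surgeon. It mentions neither the pre-operative score nor a patient effect to link the two follow-up measurements.

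Two features of the design make this worth a line of text. The population mixes elective and emergency surgery, so pre-operative EQ-5D can plausibly vary widely. The one factor named for the minimisation is contamination class, so chance differences in baseline EQ-5D between arms are not controlled by anything the article states. The only covariate modelling that the article describes, under Exploratory analysis on the primary outcome, concerns SSI and is conditional on a significant primary result. It does not reach EQ-5D.

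At stake is the width of the EQ-5D confidence interval. There is also a practical reason to settle the term in advance, because a baseline covariate added after the data have been seen is open to challenge.

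**Working it through.** **The plan's own figure.** The only stated sample size concerns SSI: 355 per arm for 12% against 6%, with "80% power and 0.05 significance level". Taking 0.05 as two-sided, with pooled variance under the null and no continuity correction:

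n = [1.960 × √(2 × 0.09 × 0.91) + 0.842 × √(0.12 × 0.88 + 0.06 × 0.94)]² / 0.06² ≈ 356 per arm.

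This agrees with 355 to within rounding. With 5% dropout, 710 / 0.95 gives 748, and 750 are planned. The point made here changes none of these figures.

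**Number analysed for EQ-5D.** Applying the same 5% loss to EQ-5D (an assumption), 750 × 0.95 = 712.5, or about 356 per arm.

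**Gain from baseline adjustment.** With correlation r between the pre-operative and follow-up scores:

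- residual variance is multiplied by 1 − r²;
- the equivalent sample-size factor is 1 / (1 − r²);
- the difference detectable at 80% power, in SD units, is √(2/356) × (1.960 + 0.842) × √(1 − r²), which is 0.210 without adjustment;
- power for a difference of 0.2 SD is Φ(0.2 / [√(2/356) × √(1 − r²)] − 1.960), which is 76% without adjustment.

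The document gives no EQ-5D standard deviation, target difference or correlation. Both r and the 0.2 SD difference are therefore assumptions, and r is shown as a range.

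| Assumed r | Variance multiplier | Variance reduction | Sample-size factor | Detectable difference (SD) | Power at 0.2 SD |
|---|---|---|---|---|---|
| none | 1.00 | – | 1.00 | 0.210 | 76% |
| 0.3 | 0.91 | 9% | 1.10 | 0.200 | 80% |
| 0.4 | 0.84 | 16% | 1.19 | 0.192 | 83% |
| 0.5 | 0.75 | 25% | 1.33 | 0.182 | 87% |
| 0.6 | 0.64 | 36% | 1.56 | 0.168 | 92% |

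These figures are for one follow-up visit and ignore clustering by surgeon. They show the order of the gain and do not predict this trial's precision.

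**Chance imbalance.** The standard error of the between-arm difference in baseline EQ-5D is √(2/356) = 0.075 SD, so its 95% range is about ±1.96 × 0.075 = ±0.15 SD. At r = 0.5, about 0.5 × 0.15 ≈ 0.07 SD of that could pass into an unadjusted follow-up difference in a given trial. Over repeated randomisations it averages to zero, so the cost is in variance and not in bias.

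**The case against.** The strongest reply is that the sentence is a summary. It says that the models include a surgeon effect, not that they contain nothing else. It does not even list treatment, so it cannot be a complete specification. Covariates for a secondary outcome are commonly left to the analysis plan, and the article promises that analyses will be pre-specified. This stands in part. A reader might infer that the plan rules out baseline adjustment, and the text does not support that. What can be said is that the only model stated for this outcome names no baseline term, although the variable is collected.

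It is also fair that EQ-5D is a secondary outcome, that its p value is declared nominal, and that the size of the gain rests wholly on assumed correlations. All of this stands and keeps the severity low.

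Two stronger readings are tempting, and the document supports neither.

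- **Length of stay.** A reader might infer that the same model would score in-hospital deaths as short, favourable stays. "Length of stay in hospital" is a secondary outcome, but the modelling sentence does not name it and nothing says how deaths enter it. The Background remark that "over one-third of postoperative deaths are related, at least in part, to SSI" is general and gives no mortality rate for this trial. If deaths were entered at the day of death, the shift in the mean difference would be the between-arm difference in death rate times the gap in mean stay between survivors and those who die. With an assumed difference of 0 to 4 percentage points and a gap of 2 to 8 days, that is 0 to 0.04 × 8 = 0.32 days. The sign reverses if those who die stay longer. Neither direction nor size can be derived from the document, and a competing-risk analysis is one acceptable choice among several.
- **QALYs.** A reader might infer that the cost-effectiveness result inherits baseline imbalance. The Cost-effectiveness Analysis section does not say how QALYs are computed or whether they are adjusted, so the inference assumes a method that is not given.

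**Conclusion.** The point holds as an improvement to the EQ-5D analysis, at low severity. The article's stated model for continuous outcomes names no baseline term, while a pre-operative EQ-5D is collected and the stated stratification uses contamination class only. Followed as written, the comparison is unbiased in expectation but less precise than it could be. Adjustment would remove 9% to 36% of the residual variance for an assumed baseline-to-follow-up correlation of 0.3 to 0.6. That range is an assumption, since the document offers no figure. Nothing in the article is miscalculated or contradictory here, and neither the sample size nor the primary analysis is affected. If the analysis plan already adjusts for baseline, the point is met.

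**What to change.** State in the analysis section, or confirm in the analysis plan: 'EQ-5D at day 5-7 and day 30-33 will be analysed in a mixed model with treatment, visit, treatment-by-visit interaction, pre-operative EQ-5D and the contamination class used at randomisation as fixed effects, and patient and surgeon as random effects.'

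The cost is a change of wording before the data are analysed. The pre-operative score is already scheduled, no new data are needed, and the sample size is unchanged.
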